## Abstract

**Background:**

Persisting abdominal complaints are common after an episode of diverticulitis treated conservatively. Furthermore, some patients develop frequent recurrences. These two groups of patients suffer greatly from their disease, as shown by impaired health related quality of life and increased costs due to multiple specialist consultations, pain medication and productivity losses.

Both conservative and operative management of patients with persisting abdominal complaints after an episode of diverticulitis and/or frequently recurring diverticulitis are applied. However, direct comparison by a randomised controlled trial is necessary to determine which is superior in relieving symptoms, optimising health related quality of life, minimising costs and preventing diverticulitis recurrences against acceptable morbidity and mortality associated with surgery or the occurrence of a complicated recurrence after conservative management.

We, therefore, constructed a randomised clinical trial comparing these two treatment strategies.

**Methods/design:**

The DIRECT trial is a multicenter randomised clinical trial. Patients (18-75 years) presenting themselves with persisting abdominal complaints after an episode of diverticulitis and/or three or more recurrences within 2 years will be included and randomised. Patients randomised for conservative treatment are treated according to the current daily practice (antibiotics, analgetics and/or expectant management). Patients randomised for elective resection will undergo an elective resection of the affected colon segment. Preferably, a laparoscopic approach is used.

The primary outcome is health related quality of life measured by the Gastro-intestinal Quality of Life Index, Short-Form 36, EQ-5D and a visual analogue scale for pain quantification. Secondary endpoints are morbidity, mortality and total costs. The total follow-up will be three years.

**Discussion:**

Considering the high incidence and the multicenter design of this study, it may be assumed that the number of patients needed for this study (n = 214), may be gathered within one and a half year.

Depending on the expertise and available equipment, we prefer to perform a laparoscopic resection on patients randomised for elective surgery. Should this be impossible, an open technique may be used as this also reflects the current situation.

**Trial Registration:**

(Trial register number: NTR1478)

## Background

The recurrence rate of patients treated conservatively for an episode of diverticulitis is approximately 25% [1]. Elective resection has traditionally been advised after a second episode of diverticulitis. It has been thought that patients with a diverticulitis recurrence are at greater risk of developing complications, have higher mortality rates and are less likely to respond to medical treatment [2].

However, recent studies have demonstrated that the number of attacks of diverticulitis is not necessarily a prevailing factor in defining the suitability of surgery. Most patients who present with complicated diverticulitis do so at the time of their first attack. Furthermore, only a fraction (5-7%) develops complicated diverticulitis during subsequent attacks [3,4]. This and the fact that operation itself carries significant morbidity and mortality, has lead to reluctance in gastroenterologists and surgeons towards elective resection after a recurrence of the disease.

However, elective resection may be an appropriate solution for a more selective group of patients who suffer greatly from their disease. Many studies have consistently shown that 40-80% remain symptomatic after conservative treatment, leading to impaired health-related quality of life (HRQoL) and increased costs due to multiple specialist consultations, pain medication and productivity losses [1]. Logically, this is also the case for patients who continue developing diverticulitis recurrences on a frequent basis. Also, these patients often remain symptomatic in between the recurrences.

In addition of possibly preventing further recurrences and complications of diverticulitis, elective resection has frequently been demonstrated to relieve persisting symptoms after an episode of diverticulitis [5,6]. Therefore, many physicians and patients seem to abandon expectant/conservative management and subsequently choose elective resection.

Both conservative and operative management of patients with persisting abdominal complaints after an episode of diverticulitis and/or frequently recurring diverticulitis are applied. However, direct comparison by a randomised controlled trial is necessary to determine which is superior in relieving symptoms, optimising HRQoL, minimising costs and preventing diverticulitis recurrences against acceptable morbidity and mortality associated with surgery or the occurrence of a complicated recurrence after conservative management.

## Methods

### Study objective

The DIRECT trial is a multicenter randomised clinical trial. The objective is to compare conservative management to elective resection of the diseased colon segment in patients with persisting abdominal complaints after an episode of diverticulitis and/or frequently recurring diverticulitis. We hypothesize that elective resection is superior in relieving abdominal complaints, preventing further hospitalisation and specialist consultation and minimising direct and indirect hospital costs against acceptable morbidity and mortality compared to conservative management.

### Study population

#### Inclusion criteria

- Age 18-75 years.

- Patients presenting with either persisting abdominal complaints and/or frequently recurring diverticulitis after a well documented (CT-scan or ultrasonography) episode of diverticulitis.

Persisting abdominal complaints may include patients with:

- continuing lower left abdominal pain AND/OR persistent change in bowel habits AND/OR persistent blood loss.

- Symptoms must exist longer than 3 months after a previous episode of diverticulitis

Frequently recurring diverticulitis is defined as:

- Three or more diverticulitis recurrences within 2 years.

- A minimal interval of 3 months between the recurrences is mandatory.

- Persisting abdominal complaints and/or frequently recurring diverticulitis must be accompanied by inflammatory changes (CT-scan or ultrasonography) in the bowel wall: Bowel-wall thickening with or without abscess.

- ASA I-III.

#### Exclusion criteria

- Patients with elective or emergency surgery for acute diverticulitis in the past.

- Patients with an absolute operation indication (perforation with purulent/fecal peritonitis, symptomatic bowel stenosis or fistula).

- Patients with colorectal malignancies.

- Patients in ASA class III who are at high risk for per- and postoperative complications due to severe co-morbidity as regarded by the surgeon and/or the patients specialists

- Patients with a psychiatric disease or other conditions making them incapable of filling out the questionnaires or completing the objective follow up tests.

### Study endpoints

#### Primary endpoint

Health-related quality of life (HRQoL) objectified primarily by the Gastro-intestinal Quality of life Index (GIQLI) and secondarily by EuroQol-5D (EQ-5D), Short-form 36 (SF-36) and Visual Analogue Score (VAS) for pain. Patients are also asked to point out on a 7 point Likert scale whether their health and complaints have improved or deteriorated in comparison to the previous assessment.

### Secondary endpoints

1. Mortality defined as:

○ *Elective surgery*: 30-days mortality.

○ *Both groups*: Mortality associated with the development of complications related to diverticulitis during follow-up.

2. Morbidity defined as:

○ Diverticulitis recurrence

○ Perforation (with purulent/fecal peritonitis)

○ Fistula

○ Symptomatic stenosis

○ Abscess

○ Stoma formation

○ Emergency surgery or re-operation

○ Peri- and postoperative complications

3. Direct health care costs. In-hospital resource use will be recorded. During follow-up medication use, general practitioner and specialist visits will be measured at baseline and regular intervals with customized questionnaires.

4. Indirect non-health care costs, using a standardised ShortForm-health and labour questionnaire (SF-H&L) at baseline and regular intervals during follow-up.

All questionnaires are asked to be filled in at baseline and 3, 6, 9, 12, 24 and 36 months after treatment

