### Treatment of Subjects

#### Conservative treatment

Patients randomised for conservative treatment are treated according to the current daily practice. In other words, conservative treatment is determined by the preferences of the treating physician. Conservative treatment may consist of expectant management, antibiotics and/or analgetics. Should there be radiologic evidence for the presence of pericolic abscesses, percutaneous drainage may be performed depending on the size and opinion of the local radiologist regarding accessibility.

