#### Elective surgery

Patients randomised for elective surgery will undergo an elective colonic resection within approximately 6 weeks. In the interval between randomisation and elective surgery, patients are treated conservatively (see above). Intentionally, a laparoscopic approach is used. The extent to which the colon is resected in the proximal direction should cover the entire macroscopically involved colon. In other words, the proximal resection line should be where no diverticula exist or at the level where a considerable decline in number of diverticula is noted. Distally, the margin of resection should be where the taenia coli splay out onto the upper rectum. After resection a primary anastomosis will be performed between the distal colon and rectum.

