### Data collection

Data are collected by a local research fellow and/or treating physician at baseline, postoperatively (if randomised for elective resection), during outpatient visits and in case of adverse events leading to hospitalisation during follow-up. Case record forms on paper are used and faxed to the data manager.

Patients are asked to fill out HRQoL questionnaires at baseline. These questionnaires, as well as resource use and productivity losses questionnaires, are also sent to the patients at 3,6,9,12,24 and 36 months follow-up.

Data integrity will be checked when receiving the questionnaire. Any missing items will be collected by contacting the patient by telephone. Reminders (including a new copy of the questionnaire) will be send after two weeks.

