### Statistical analysis

The statistical package SPSS will be used for analysis. All analyses will be performed according the intention to treat principle.

Baseline characteristics will be described as means and standard deviations. Large differences between treatment groups will be analysed with an independent Student's T-test to verify significance (p-value < 0.05). Significant differences will be adjusted for in the final analysis.

The primary outcome will be analysed using mixed linear models with random effects. The covariates of the random part of the model will be determined using restricted maximum likelihood estimation (REML) and selected on the basis of Akaike Information Criterium (AIC). For the fixed part, models will be constructed containing either the treatment effect adjusted for time with or without an interaction term of these components. The models will be compared using AIC. Missing data will be imputed using multiple imputation.

The estimates of the final model will be used to test whether or not there is a clinical difference between the treatment groups. As described before, the MID is 10 points on the GIQLI scale. Therefore, the MID will be subtracted from the estimated difference between treatment groups and tested with Wald's test against a p-value of 0.10.

Additionally, the 7 point scale reflecting self-reported improvement of complaints over time, will be used to confirm whether the assumption of MID being the equivalent of half a standard deviation, holds.

Categorical outcome measures will tested using the chi-square test (p-value < 0.05) and described as percentages and counts.

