### Economic evaluation

The cost analysis will be performed form a societal perspective including total direct health care costs and indirect non-health care costs (productivity losses).

Direct health care costs include costs related to hospitalization, imaging, blood tests, colonoscopy, medication, interventions, operations, consultations, complications and primary health care contacts. On an individual patient basis, resource use will be recorded. Subsequently, by multiplying resource use with unit price, actual costs per patient will be calculated. Unit costs will be derived from the Dutch costing manual or determined in co-operation with hospital administration.

Health care consumption including general practitioner or specialist visits and medication use will be assessed using customised questionnaires and case report forms.

Indirect non-health care costs include sick leave from paid work, own expenses of patients and time and travel costs. Sick leave from paid work will be assessed using the ShortForm-Health and Labour questionnaire. The remaining indirect non-health costs will be assessed using customised questionnaires to be completed by participants.

The cost-effectiveness will be expressed as incremental costs per quality-adjusted life year (QALY) gained. QALY gains over time will be assessed using the EQ-5D classification system as completed by patients, in combination with pre-defined value sets for all possible health states. The time perspective of the analysis will be 3 years.

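### Questionnaires are timed from treatment, but only the surgical arm has a datable treatment, so the two arms have no stated common time origin

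*Protocol article*

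**What the plan says.** The schedule appears twice in the protocol article. Secondary endpoints counts it from treatment: "All questionnaires are asked to be filled in at baseline and 3, 6, 9, 12, 24 and 36 months after treatment". Data collection repeats the months for the quality-of-life, resource-use and productivity questionnaires, which "are also sent to the patients at 3,6,9,12,24 and 36 months follow-up", and does not say when follow-up starts.

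For the surgical arm, the Elective surgery section states: "Patients randomised for elective surgery will undergo an elective colonic resection within approximately 6 weeks". It adds: "In the interval between randomisation and elective surgery, patients are treated conservatively". For the comparator, the Conservative treatment section leaves care to the treating physician and gives no start date: "Conservative treatment may consist of expectant management, antibiotics and/or analgetics".

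Two analysis statements depend on this clock. Statistical analysis says "All analyses will be performed according the intention to treat principle" and describes the fixed part of the primary model thus: "models will be constructed containing either the treatment effect adjusted for time with or without an interaction term of these components". Economic evaluation says "The time perspective of the analysis will be 3 years". Neither section defines time zero.

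**The concern.** An event that exists in one arm only cannot serve as the time origin for both. Resection has a date. Conservative care is a continuing policy that may amount to watchful waiting, so there is no comparable date from which to count. Followed literally, the rule ties the visit clock to the allocated arm and, within the surgical arm, to whether and when the operation took place.

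Two groups are left in doubt. A patient allocated to surgery who is never operated on has no date from which to schedule questionnaires. A conservative patient who later proceeds to resection, which the Randomisation section allows, has an ambiguous one, because the article does not say whether the clock restarts. Both belong in an intention-to-treat comparison, and such a comparison works best when the visit schedule does not depend on treatment received.

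The primary GIQLI comparison adjusts for time, and the EQ-5D behind the QALYs and the cost questionnaires follow the same schedule. If nominal month 3 means different elapsed time since randomisation in the two arms, adjusting for nominal time does not remove the difference. The weeks on the waiting list would also lie between the baseline questionnaire and the start of the surgical questionnaire clock.

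**Working it through.** The plan gives no figure for this offset, so there is none to reproduce. The check is date arithmetic.

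**Inputs**
- Nominal visits: 3, 6, 9, 12, 24 and 36 months (Secondary endpoints; Data collection).
- Wait from randomisation to resection: up to about 6 weeks (Elective surgery). This is an approximate upper limit, so 2, 4 and 8 weeks are assumed as a range around it.
- Start of the conservative clock: randomisation. This is an assumption; the article defines no start for that arm.
- Horizon of the economic evaluation: 3 years.

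**Offset.** For a wait of w weeks, the offset in months is d = w × 7 / 30.4375.
- w = 2: 14 / 30.4375 = 0.46 months
- w = 4: 28 / 30.4375 = 0.92 months
- w = 6: 42 / 30.4375 = 1.38 months
- w = 8: 56 / 30.4375 = 1.84 months

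**Visits in the surgical arm with surgery at week 6.** Under the treatment clock, time from randomisation is t + d and the relative offset is d / t. If visits are counted from randomisation instead, time since resection is t − d.

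| Nominal month t | Treatment clock: months from randomisation (t + d) | Offset as % of t | Randomisation clock: months since resection (t − d) |
|---|---|---|---|
| 3 | 4.38 | 46.0 | 1.62 |
| 6 | 7.38 | 23.0 | 4.62 |
| 9 | 10.38 | 15.3 | 7.62 |
| 12 | 13.38 | 11.5 | 10.62 |
| 24 | 25.38 | 5.7 | 22.62 |
| 36 | 37.38 | 3.8 | 34.62 |

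Under the stated assumption the conservative arm's visits fall at t itself, so d is the gap between arms at every visit. At month 3 the gap runs from 15% of nominal time (2-week wait) to 61% (8-week wait).

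**Economic horizon.** A 6-week wait is 6 / 52.18 = 0.115 years, and 0.115 / 3 = 3.8% of the 3-year horizon. That share would lie before the surgical questionnaire clock starts.

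**After the change.** With both arms counted from randomisation, the gap between arms is 0 at every visit. The required sample size does not depend on the time origin and is unchanged.

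**The case against.** The strongest reply is that the article never says the arms are measured on different dates. It uses one loose phrase about treatment, while the operational section speaks only of follow-up. The Patient safety section refers to inclusion followed by half a year of follow-up, which is compatible with a clock that starts at inclusion. The abstract gives a single three-year follow-up for both arms. The full protocol, which is not shown, may settle time zero. This stands in part: a reader might infer an established difference between the arms, and the document does not support that. The offset is what the Secondary endpoints sentence implies if the conservative clock starts at randomisation. But the sentence is a stated rule, not an omitted detail, and reading Data collection as running from randomisation would put it in conflict with that rule.

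It is also tempting to say that the later surgical visits favour surgery, because patients enrolled while symptomatic tend to improve. The document gives no figure for such drift, and the Background reports that 40-80% remain symptomatic after conservative treatment. Nor is it shown that recurrences or hospital costs are counted over windows of unequal length: the sentence governs questionnaires only, and a longer window would in any case add events and costs to the surgical arm.

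Nor is the waiting period unobserved. There is a baseline questionnaire, and case record data are collected at outpatient visits and at adverse events leading to hospitalisation. Finally, intention to treat is not breached as written: unoperated patients lack a scheduling date, but nothing says they are excluded. All of these limits stand. None of them supplies the missing common origin.

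**Conclusion.** The concern holds as a defect in the stated time origin, and it should be corrected. The wording gives the surgical arm a clock that starts at operation, gives the conservative arm no defined start, and leaves patients allocated to surgery but not operated on without a time zero.

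The size is conditional on two things: a conservative clock that starts at randomisation, and the actual wait. At the approximate 6-week limit the shift is material at the early visits and small at 24 and 36 months; shorter waits reduce it in proportion. No visit is named as the primary time point, so the month-3 figure shows the largest relative shift and does not measure the effect on the overall mixed-model result. The article does not permit a statement on the direction or amount of bias in GIQLI, QALYs or costs.

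**What to change.** In Secondary endpoints and in Data collection, state that all questionnaires are due at 3, 6, 9, 12, 24 and 36 months after randomisation in both arms, whether or not and whenever surgery took place. In Economic evaluation, start the 3-year cost and QALY horizon at randomisation. Record the date of surgery and use time since surgery for description only.

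The cost is a change of wording and of the mailing schedule. The downside is that the month-3 questionnaire would fall about 1.6 months after resection if surgery is at week 6, so it would show early recovery and not the settled result. That belongs in a comparison of the two strategies from the point of allocation, and the later visits describe the longer-term outcome.

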### Sample size

The sample size calculation is based on the minimum important difference* (MID) of the GIQLI score. The MID can be estimated by taking half a standard deviation of a quality of life instrument [7,8].

Based on the studies of Forgione et al and Zdichavsk et al the MID of the GIQLI score is estimated at 10 points [5,6]. They also demonstrated that patients improve with 10 points on the GIQLI score one month to one year after elective resection (111 ± 20.4 and 105.8 ± 15.5) for diverticulitis compared to preoperatively (100 ± 22.1 and 95.3 ± 21.4). In conclusion, a difference of 10 points corresponds with the MID and the expected improvement after elective resection.

To demonstrate this difference using an independent t-test (alpha = 0.05, delta = 10, sigma = 21, power = 0.9) approximately N = 97 patients per group are needed for this study. Therefore a total study population of 194 patients is required to attain statistical significance.

To compensate for a potential loss to follow-up of 10%, 214 patients will be included.

** Minimum important difference (MID): The smallest difference in score in the domain of interest which patients perceive as beneficial and which would mandate, in the absence of troublesome side effects and excessive cost, a change in the patient's (health care) management*.

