#### Randomisation (figure 1)

**Figure 1 F1:**
[figure not shown]
Flowchart DIRECT trial

All patients presenting themselves with persisting abdominal complaints after an episode of diverticulitis and/or a third (or more) diverticulitis recurrence, require to have had a recent radiological examination of the abdomen. Preferably a CT-scan is used. However, ultrasonography may also be used on the condition that bowel wall thickening and abscess size can be assessed accurately. Colonoscopy may be performed on indication to exclude malignancy.

If all inclusion criteria are met, patients are informed about the study protocol by their treating physician. They are given a 3 day reflective period, together with the information package. After the reflective period, the patient is contacted and asked for participation. If the patient decides to take part in the trial, he/she is invited to the local hospital to sign the informed consent. After receiving this consent form, randomisation will be performed centrally by the study coordinator using block randomisation (block size 6) stratified for center and inclusion criteria (persisting abdominal symptoms or frequent recurrences).

Both patients in the conservative and elective resection group will be treated conservatively in case of events during follow-up unless there is an absolute indication for surgery according to the treating physician (e.g. fistula, symptomatic stenosis, perforation with purulent/fecal peritonitis). In addition, in case of persisting abdominal symptoms during follow-up (in the conservative group) which are regarded as unbearable by both patient and treating physician, the treating physician may consult an independent event adjudication committee. The independent committee will advise the treating physician whether or not to abandon conservative management and proceed to elective resection. The final decision is made by the treating physician.

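### The 90% power takes a before-after gain in operated patients as the expected between-arm difference and allows nothing for permitted crossover, so it holds only for a true ITT difference of about 9.8 to 9.9 points or more

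*Protocol article*

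**What the plan says.** The Sample size section first bases the calculation on the MID of the GIQLI, estimated at 10 points. It then brings in two published surgical series: "They also demonstrated that patients improve with 10 points on the GIQLI score one month to one year after elective resection". The means rose from 100 to 111 and from 95.3 to 105.8. From this it concludes that "a difference of 10 points corresponds with the MID and the expected improvement after elective resection".

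The 10 points become the delta of a two-arm comparison ("To demonstrate this difference using an independent t-test") with "alpha = 0.05, delta = 10, sigma = 21, power = 0.9", and "approximately N = 97 patients per group are needed for this study". The only inflation is for attrition: "To compensate for a potential loss to follow-up of 10%, 214 patients will be included".

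Under Randomisation, patients in the conservative arm may be operated on for an absolute indication. For symptoms that both patient and physician find unbearable, the physician may consult an independent committee, which will "advise the treating physician whether or not to abandon conservative management and proceed to elective resection". The final decision is the physician's. The Background remarks of current practice that "many physicians and patients seem to abandon expectant/conservative management and subsequently choose elective resection". The Statistical analysis section applies ITT to all analyses. Follow-up runs to 36 months.

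**The concern.** Two different quantities are treated as one. A gain from before to after surgery is a change within one arm. The delta of an independent t-test is a difference between arms. They coincide only if the conservative arm has a mean change of zero. The protocol neither states nor subtracts any such change, although conservative patients receive care and are enrolled because they have symptoms, so some improvement is plausible.

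Crossover acts in the same direction. If surgery helps, conservative patients who are operated on move towards the surgical arm, and ITT counts them where they were randomised. The protocol describes this route but makes no allowance for it.

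What is at stake is how a null result would be read. A non-significant ITT comparison would be taken to come from a trial with 90% power against the effect its authors expected. If the expected effect of surgery is 10 points and there is any dilution, the expected ITT difference is below 10 and the power against it is lower than stated.

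**Working it through.** **Inputs from the Sample size section.** Alpha 0.05 (two-sided assumed, as sidedness is not stated), delta 10, sigma 21, power 0.90, 97 per group, 194 in total, 214 enrolled. Pre- and postoperative means: 100 and 111; 95.3 and 105.8.

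**Step 1: the plan's own figure.** n per group = 2 × (1.96 + 1.2816)² × (21/10)² = 92.7, so 93 by the normal approximation. The noncentral t gives 93.6, so 94. The plan states approximately 97. With sigma 21.4, one of the SDs printed in the same section, the normal approximation gives 96.2 (97 rounded up) and the t-test 97.2, so a rounded sigma is a likely explanation. The three extra patients per group raise power.

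**Step 2: attrition.** 194 × 1.1 = 213.4, so 214; dividing instead, 194/0.9 = 215.6, so 216. After 10% loss, 214 × 0.9 = 192.6, or about 96 per group.

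**Step 3: power at the stated target.** For a true ITT difference of 10 with sigma 21, t-test power is 0.910 at 97 per group and 0.907 at 96. The stated 90% is reproduced.

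**Step 4: the margin.** The smallest true difference giving 90% power is 9.82 points at 97 per group and 9.88 at 96. If the undiluted benefit is 10 points, the room is 10 − 9.82 = 0.18 or 10 − 9.88 = 0.12 points. That is a conservative-arm gain of 0.1 to 0.2 points, or crossover of 1 to 2%.

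**Step 5: where the 10 points come from.** 111 − 100 = 11.0 and 105.8 − 95.3 = 10.5. Both are within-patient-group changes without a control. If g is the mean conservative-arm gain and c the proportion crossing over with full benefit, the expected ITT difference is (10 − g) × (1 − c). The plan's delta corresponds to g = 0 and c = 0.

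**Step 6: power away from that corner.** The document gives neither g nor c, so the values below are assumptions. Single-time-point t-test, sigma 21, 97 per group:

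| True ITT difference | Arises from, for example | Power |
|---|---|---|
| 10 | g = 0, c = 0 | 0.91 |
| 9 | c = 10%, or g = 1 | 0.84 |
| 8 | c = 20%, or g = 2 | 0.75 |
| 7 | c = 30%, or g = 3 | 0.64 |
| 6.4 | g = 2 and c = 20%: 8 × 0.8 | 0.56 |

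**Step 7: what baseline adjustment could recover.** Adjusting for a baseline score correlated r with the outcome reduces the SD to 21 × √(1 − r²). With r = 0.5 (assumed), this is 21 × 0.866 = 18.2. Power at 8 points is then about 0.86 instead of 0.75.

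**The case against.** The strongest reply is that delta is declared first as the MID. Powering an ITT comparison on the smallest difference worth acting on is valid whatever effect is expected, and at that difference the design has about 91% power. This stands. A reader might infer that the trial does not deliver its stated power. The document does not support that: the shortfall is conditional on an ITT difference below 10. What remains is that the section does not stop at the MID; it also offers 10 points as the expected effect, on uncontrolled data.

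Second, no crossover rate or conservative-arm change is given. The Background remark concerns practice outside the trial, and within it surgery in the conservative arm is restricted. The Background also says 40-80% stay symptomatic after conservative treatment, so improvement is not certain. Patients who cross over late would dilute the early visits less than the simple model assumes. All of this stands, so one cannot claim that the expected ITT difference is well under 10.

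Third, the planned analysis is a mixed model over six post-baseline assessments, not a single t-test. As an illustration, averaging six visits with equal between-visit correlation multiplies the variance by (1 + 5r)/6. At 8 points this gives power of 93%, 86% and 82% for r = 0.5, 0.7 and 0.8. These correlations are assumptions too, but they show that the t-test figures may be pessimistic. The article, however, rests its 90% on the t-test, and its Statistical analysis section promises adjustment only for baseline variables that differ significantly. That section also plans a test of the difference minus the MID at 0.10. This is a separate question, and the power figures here do not describe that test.

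A reader might also see an arithmetic error in 97 or 214. The first is stated as approximate and errs on the safe side, and the second is two patients from 216. Neither costs meaningful power.

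**Conclusion.** The concern holds as a fault in how delta is justified and how power is reported. The plan equates a within-arm gain with a between-arm expectation and makes no allowance for a crossover route that it permits under ITT. The 90% holds for a true ITT difference of about 9.8 to 9.9 points or more, so the margin against dilution is close to nil.

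The loss grows quickly below that, to 75% at 8 points. These sizes rest on sigma 21, a two-sided single-time-point t-test, a 10-point undiluted benefit, full benefit in every patient who crosses over, and rates of crossover and conservative-arm change that are assumed. The direction follows from the design if surgery helps or the conservative arm improves; the amount cannot be settled from the document.

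**What to change.** Keep enrolment at 214. In the Sample size section:

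- State that 10 points is the MID to be detected, and remove the suggestion that it is the expected ITT difference.
- Replace the single 90% with power over a stated range, for example 0 to 30% crossover and 0 to 4 points of conservative-arm improvement, with the assumptions labelled.
- Name the sigma used: 21 gives 94 per group by t-test, and 97 corresponds to about 21.4.

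In the Statistical analysis section, commit in advance to adjusting the GIQLI model for baseline GIQLI, whether or not the arms differ on it, and base the power statement on that model with its assumed correlation stated.

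Baseline GIQLI is already collected, so no extra patients or data are needed. The cost is recalculation and a less favourable stated power over part of the range.
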